**Fig. 3 Fig3:**
[figure not shown]
Key mediation pathways to be tested in the Paediatric Autism Communication Therapy-Generalised (PACT-G) Trial mechanism study

We will also repeat these four steps using researcher BOSCC as the outcome variable in place of the ADOS. Since all the measures are continuous, the indirect effects are calculated by multiplying relevant pathways and bootstrapping is used to produce valid standard errors for the indirect effects. All analyses will adjust for baseline measures of the mediators (BOSCC/DCMA), outcome (ADOS) and putative measured confounders. Mediation analyses are potentially biased by measurement error in mediators and hidden confounding between mediators and outcomes; we will build on our previous methodological and applied work in this context to include repeated measurement of mediators and outcomes to account for classical measurement error [15] and baseline confounding [51]. We will investigate the sensitivity of the estimates to these problems and that of unmeasured confounding using instrumental variable (IV) methods [52] with baseline covariate by randomization interactions as potential instruments [52].

Treatment compliance in the education setting is likely to be more variable than the high levels achieved with parents. We will estimate a complier average causal effect (CACE) estimate using instrumental variable methods, considering the extent of education-setting opt-in as a measure of compliance and randomisation as the instrumental variable.

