## Methods/design

### Aims

The PACT-G study has two aims. Firstly, it will test whether the extended PACT-G social communication intervention protocol, using targeted enhancement strategies within home and education settings, improves transmission of treatment effect to:

(1) Researcher-assessed autism symptom outcome; (2) Autism symptoms and functional adaptation in home and education settings. This objective will be tested using blinded measures maximising the ability to detect meaningful change (see ‘Measures’ below) and evaluated by analysis at trial endpoint.

The second aim is a mechanism analysis that will use the experimental trial to illuminate core processes of generalisation of specific acquired competencies in autism across context: (1) We will build on the mediation analysis from our previous PACT Trial (see above) to test mediation of the generalised treatment effect in home and school, (2) We will test how effects in naturalistic contexts may combine to enhance transmission of effect to research-assessed symptoms in a standardised test setting. In doing this, we will use the pre-specified measures of mediation which were successful in our previous MRC PACT trial.

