## Statistical analysis

### Sample size calculations

The PACT trial showed an effect of ES 1.22 (0.85, 1.59) on parental synchrony (DCMA), which mediated 70% of the ES 0.41 (0.08, 0.74) on child communication, which in turn mediated 72% of the ES 0.24 (0.59, 0.11) on symptom outcome (ADOS). The intervention strategies in the PACT-G trial are specifically targeted to enhance generalisation of the child communication to increase effects on primary outcome in home, education and research settings. Therefore, we expect the ES for the symptom outcome to be substantially above 0.24 and clinically meaningful (see above). Power was calculated using the sampsi command in Stata for an analysis using analysis of covariance (ANCOVA) with alpha = .05, with pre and post measures correlated at .67 (based on PACT trial). With 110 cases followed up in each group (70/70 pre-school and 40/40 school-age) 80% power is retained for ES = 0.28 and 90% power for ES = 0.33. Allowing for 10% attrition (compared to 4% in PACT) we propose to recruit 244 families (~ 82/site − 52 pre + 30 school-age).

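### Continuous measures alone do not justify multiplying paths: the product also assumes no treatment-by-mediator interaction, which the protocol article does not state

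*Protocol article*

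**What the plan says.** Phase 2 of the Statistical analysis section lists four mediation steps, using parametric regression and then a structural equation model over paths a to f. Reading the letters from that list, a and c run from treatment to the home and education mediators, b from home to education, e and d from those mediators to the ADOS, and f is the direct path. The steps are repeated with the researcher BOSCC as outcome. The text below Fig. 3 gives the estimator and its reason: "Since all the measures are continuous, the indirect effects are calculated by multiplying relevant pathways". It then names measurement error in the mediators and hidden confounding as the threats.

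The second aim (Aims) reads: "We will test how effects in naturalistic contexts may combine to enhance transmission of effect to research-assessed symptoms". The first aim also speaks of improved transmission of treatment effect. Sample size calculations describes the strategies as "specifically targeted to enhance generalisation of the child communication to increase effects on primary outcome". Phase 2 says the original trial showed attenuated generalisation, which PACT-G is meant to enhance.

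Phase 3 plans moderation of the paths by age group and by a wider list whose examples are child characteristics. The only interactions with randomisation in Phase 2 involve baseline covariates, as candidate instruments. Arm is not named as a moderator of path d or e.

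**The concern.** A product of coefficients is an indirect effect under two conditions: the mediator and outcome models are linear, and treatment does not change the slope of outcome on mediator. Continuous measurement secures neither. The second condition deserves attention here because the therapy aims to help acquired skills carry over into other settings. One plausible form of that is a steeper mediator-to-symptom slope under PACT-G than under TAU.

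If the slopes differ and one common slope is fitted, the indirect effect and path f are both misallocated. The proportion mediated, which the article uses to describe the original trial, would be distorted. The slope difference itself would have no separate estimate.

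**Working it through.** **The plan's own figures.** Sample size calculations assumes an ANCOVA at the 5% level, 110 analysed per arm and a baseline-to-outcome correlation of 0.67. The ANCOVA SD factor is √(1 − 0.67²) = 0.742. Taking alpha as two-sided, 110 per arm gives 79.9% power at 0.28 and 90.9% at 0.33, matching "80% power is retained for ES = 0.28 and 90% power for ES = 0.33". Attrition: 220/0.9 = 244.4, against 244 stated. The design figures reproduce, so 110 per arm is used below. Allocation is 1:1 (122/122, Abstract).

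**Algebra for one mediator link.** Let T be arm and let M be measured from the TAU mean:

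- M = aT + error
- Y = fT + (b₀ + dT)M + error, where d is the slope difference between arms
- Total effect = f + a(b₀ + d)
- Pure natural indirect effect = a·b₀; total natural indirect effect = a(b₀ + d)
- Common fitted slope = b₀ + w·d, where w is the treated arm's share of within-arm mediator variance; at 1:1, w = V₁/(V₁ + V₀)
- Product of paths = a(b₀ + w·d)
- Fitted direct path = f + a·d(1 − w)

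Measured against the total natural indirect effect, a share 1 − w of the gain a·d moves to path f:

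| V₁/V₀ | w | Kept in product | Moved to path f |
|---|---|---|---|
| 0.5 | 1/3 | 33% | 67% |
| 1 | 1/2 | 50% | 50% |
| 2 | 2/3 | 67% | 33% |

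A simulation with 110 per arm, 3,000 replicates and adjustment for baseline mediator and outcome gave moved shares of 0.66, 0.50 and 0.33 at d = 0.22. With d = 0 and equal variances the product averaged 0.174 against a true 0.173, so it is unbiased without interaction.

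The 50% is specific to one link. In a two-link chain with both slopes doubled and equal variances, the true product is 4 times the base and the common-slope product 1.5² = 2.25 times, so (4 − 2.25)/(4 − 1) = 58% of the gain is lost.

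**Can Sample size calculations supply d?** It gives the earlier trial's effect on child communication as 0.41, mediating 72% of 0.24. Then:

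- indirect effect = 0.72 × 0.24 = 0.1728
- slope = 0.1728/0.41 = 0.421
- direct effect = 0.24 − 0.1728 = 0.0672

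Two scenarios reach the same design effect sizes:

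1. *All gain in the slope.* Keep a = 0.41 and assume 0.421 is the TAU slope. Effect size 0.28 needs d = (0.28 − 0.24)/0.41 = 0.098; 0.33 needs d = (0.33 − 0.24)/0.41 = 0.220. At 0.33 with equal variances, the total indirect effect is 0.263, the product 0.218 and fitted path f 0.112 instead of 0.067. The proportion mediated is 66% instead of 80%.
2. *All gain in the mediator.* Keep slope 0.421 and direct effect 0.0672. Effect size 0.28 needs a = 0.2128/0.4215 = 0.505; 0.33 needs a = 0.2628/0.4215 = 0.62. Here d = 0 and the product is correct.

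The article's figures do not distinguish these, so scenario 1 is only an illustration.

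**Power to detect d.** On assumed unit-scale measures with equal variances, simulated power at d = 0.22 was 58%. A standard error of about 0.097 gives 0.22/0.097 = 2.27 and 62% power; at d = 0.10, 0.10/0.097 = 1.03 and about 18%.

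**The case against.** The strongest reply is that the article never says the d and e slopes should be steeper under PACT-G than under TAU. The second aim is about home and school effects combining; the Abstract and Discussion speak of additive effects, and the step 4 model covers that. Phase 2 describes enhancement as more functionally relevant contexts at home and better communication with education staff, which can be modelled as larger mediator effects plus the home-to-education route. The first aim is to be evaluated at trial endpoint. All of this stands: a slope change is a plausible reading of the hypothesis, not the stated one.

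A reader might infer that enhanced transmission is never estimated. The article does not support that. A common slope retains part of any slope gain and the additional routes are modelled; what has no named place is a separate estimate. A common slope is itself inferred from the product rule and from the lack of an arm-specific term. The statistical analysis plan is not available here and may add one.

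A reader might also take 0.10 to 0.22 as the expected interaction. That is the gap between PACT-G's design effect and the earlier trial's result. Comparing PACT-G with TAU cannot identify a contrast with the original therapy, even with an interaction term.

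The objection on size also has weight. In scenario 1 the misallocation at equal variances is 0.02 to 0.045. Sampling error in path a alone gives the product a standard error of about 0.53 × √(2/110) = 0.07 (assuming unit SD, slope 0.53 and no baseline adjustment). This limits the urgency, but does not make continuity a valid reason for the estimator.

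**Conclusion.** The concern holds in a limited form. The article rests its indirect-effect estimator on a reason that is not sufficient, leaves the no-interaction assumption unstated, and names no analysis that would check it. If the mediator-to-symptom slope differs by arm, part of the gain moves to path f: 50% under 1:1 allocation, equal within-arm mediator variance and a single link, and 33% to 67% for treated-to-control variance ratios of 2 to 0.5. These shares count the interaction component as mediated, as the total natural indirect effect does.

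Whether the slopes differ, and by how much, cannot be derived from the article. If they do not differ, the product is unbiased. The primary ANCOVA and the total treatment effect are unaffected in either case. This is an inexpensive improvement to a secondary but stated aim.

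**What to change.** 1. Replace the continuity justification with the assumptions actually used: linear models and no treatment-by-mediator interaction.
2. In the ADOS and researcher-BOSCC equations of steps 1, 2 and 4, add arm-by-home-mediator (path e) and arm-by-school-mediator (path d) terms as a pre-specified sensitivity analysis. Report the slope differences with 95% confidence intervals, not as a pass/fail gate.
3. Keep the simple product alongside.
4. Where interaction is evident, report pure and total natural indirect effects for the home mediator. Report natural effects through the school mediator only with the added assumptions stated: the home mediator affects the school mediator (path b), so it is a confounder that treatment itself changes.

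The cost is wording and model specification, with no new data. Intervals for the indirect effects will be wider, and power for modest slope differences is limited, so a wide interval must not be read as evidence of equal slopes. If the interaction terms are carried into the planned instrumental-variable sensitivity analysis, each adds a second endogenous variable for the covariate-by-randomisation instruments to identify; that should be acknowledged.

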### Design

A three-site, two-group, randomised controlled trial of the experimental treatment plus TAU compared to TAU alone. Children aged 2–11 years with core autism will be recruited to the trial in the local areas following referral via clinical specialists, education professionals and consented databases. After consent families will be randomised in three sites around the UK to receive either the PACT-G social communication intervention in addition to TAU or TAU alone**.** Assessments are administered on entry (baseline) to the trial, at the 7-month midpoint and at the 12-month endpoint. There will be an embedded mechanism study to test mediation hypotheses and illuminate the basic science underpinning the understanding of generalisation impairments in autism.

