#### Parent sessions

Based on what was found to be most effective in the original PACT trial, parents will receive 12 intervention sessions. Prior to starting the intervention, a home visit is conducted to introduce the intervention to the parents, explore the family context and set expectations. The therapy sessions are delivered in the home. Subsequent sessions alternate between home-based sessions and Skype/telephone-delivered consultation. Delivery is flexible in accordance with the needs of the family. This approach will assist generalisation of new skills development in the home setting. Clinical and research experience indicates that these session formats are popular with parents [22]. Each parent session begins with a discussion of progress made since the last session. The parent and child are then filmed whilst playing for 10 min. Immediately after this the therapist and parent watch the film, or during Skype sessions the therapist and parent watch a 1–2 min parent-made video of a home-based practice session routine. The therapist facilitates the parent to identify actions that lead to child communication and to adopt PACT-G strategies in their interaction with the child. Parents are assisted to set goals for themselves, based on the interaction strategies discussed. The parent and therapist discuss the opportunities to practice these strategies each day outside of therapy sessions and parents are asked to make time to practice them daily for half an hour.

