#### Education-setting sessions

In most cases, therapy in the educational setting begins after the parent has commenced therapy at home. The start times and duration of education-based therapy are flexible to fit around the school-term schedule. In the education setting PACT-G sessions will be delivered to trained learning support assistants (LSA), who are staff with a specific remit to assist children with special educational needs to access the curriculum- and broader school-based activities, e.g. mealtimes, etc. LSAs and other education staff receive an initial training session to introduce them to PACT-G. The education-based intervention then consists of therapist-LSA sessions that mirror the therapist-parent sessions in the home. Videos are made of the LSA and the child and are used to coach the LSA in the use of PACT-G strategies in a similar procedure to the parent. The LSA then implements these with the child daily in class time. There are a maximum of 12 therapist-LSA sessions over 6 months, alternating in-school visits and Skype/telephone consultation. PACT-G strategies are expected to be integrated in a complementary way with other communication strategies that may already be in use in the school.

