#### Phase 2 – Mechanisms’ evaluation

Mediation analysis [15] gave detailed insight into an attenuated generalization in the original PACT trial across change in person, task and context (as above and Fig. 1). In the PACT-G trial we enhance generalisation *into home* by keeping parental dyadic cues constant, but increasing functionally relevant interaction contexts; and *into education* by enhancing relevant communication with education staff (LSA). The mechanism study will investigate the mediation process in this model and, through that, illuminate key basic knowledge about generalisation of acquired skills in autism. Some of the pathways of interest are illustrated in Fig. 3. If the efficacy analysis shows significant between-group differences in the mediators (DCMA and/or BOSCC at home (path a) and in education contexts (path c)), then we will use parametric regression models to:Test for mediation of the intervention on primary symptom outcome (ADOS) through DCMA and/or BOSCC at home (paths a,e,f)Test for mediation of the intervention on primary symptom outcome through DCMA and/or BOSCC in the education setting (paths c,d,f)Test for mediation of intervention on DCMA and/or BOSCC in education setting through DCMA and/or BOSCC at home (paths a,b,c)Use structural equation modeling to examine multiple pathways through DCMA and/or BOSCC at home and in the education setting to primary symptom outcome (paths a–f)

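### The Phase 2 CACE uses randomisation as sole instrument for education-setting opt-in, but randomisation also delivers home therapy, so the exclusion restriction conflicts with the protocol's own causal model

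*Protocol article*

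**What the plan says.** The last paragraph of Phase 2 – Mechanisms' evaluation gives the reason for the analysis: "Treatment compliance in the education setting is likely to be more variable than the high levels achieved with parents". It then fixes both parts of the estimator, "considering the extent of education-setting opt-in as a measure of compliance and randomisation as the instrumental variable". It names no outcome for the CACE and does not say in words whose effect, or the effect of what, is being estimated.

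Other sections describe what randomisation delivers:

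- Design: a "randomised controlled trial of the experimental treatment plus TAU compared to TAU alone". The contrast is the whole package.
- Parent sessions: "parents will receive 12 intervention sessions".
- Education-setting sessions: "There are a maximum of 12 therapist-LSA sessions over 6 months". In most cases "therapy in the educational setting begins after the parent has commenced therapy at home".
- Phase 2, list of mediation tests: the first test runs from the intervention to ADOS by way of the home interaction measures (paths a, e and f).

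Phase 2 does name further instruments, "with baseline covariate by randomization interactions as potential instruments", but it assigns them to the sensitivity analysis of the mediation models, not to the CACE.

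**The concern.** An instrumental-variable CACE with randomisation as the only instrument needs the exclusion restriction: allocation may change the outcome only by changing the named compliance variable. Here that variable is education opt-in. A PACT-G child whose school engages little or not at all still has a parent who is offered the home sessions, usually begun before the school work, and the protocol expects parents to comply well. Such a child counts as untreated on the compliance scale but has been treated.

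The estimator divides the whole between-group difference by education uptake. Any benefit that reaches poorly complying children through home therapy is loaded onto the education variable, and the inflation grows as education uptake falls. At stake is the interpretation of one secondary mechanism estimate.

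**Working it through.** **The plan's own figures.** The protocol gives no number for the CACE. Its sample-size figures reproduce: with 110 per group, residual SD √(1 − 0.67²) = 0.742 and two-sided alpha 0.05, power is 79.9% at an effect size of 0.28 and 90.9% at 0.33, against 80% and 90% stated. The 0.28 is a detectable difference for the whole randomised contrast, so it is not used below as a home effect.

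**Inputs.**

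- h, home effect delivered by allocation whatever the education uptake: 0.24 SD for illustration. Sample size calculations reports this for ADOS in the earlier parent-mediated PACT trial.
- e, effect of full education uptake: unknown, left free.
- p, education uptake in the PACT-G arm (proportion, or mean of a 0–1 scale): not in the document, so 0.5 to 1.0 is assumed.
- Uptake in the TAU arm: taken as 0, since trial therapists treat no TAU patients (Training and fidelity of treatment).
- h and e are taken as additive, with h the same in education compliers and non-compliers. Effects are written so that positive means benefit.

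**Estimand.**

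1. Intention-to-treat difference = h + p·e.
2. Difference in education uptake between arms = p − 0 = p.
3. CACE = (h + p·e)/p = e + h/p.
4. Read as the education effect (target e): bias = h/p.
5. Read as the package effect in education opt-ins (target h + e): bias = e + h/p − (h + e) = h(1 − p)/p.

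**Results with h = 0.24.** Neither bias depends on e.

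| p (assumed) | Bias, education reading: 0.24/p | Bias, package reading: 0.24(1 − p)/p |
|---|---|---|
| 0.5 | 0.48 | 0.24 |
| 0.6 | 0.40 | 0.16 |
| 0.7 | 0.34 | 0.10 |
| 0.8 | 0.30 | 0.06 |
| 0.9 | 0.27 | 0.03 |
| 1.0 | 0.24 | 0.00 |

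A simulation of 2,000,000 records with h = 0.24, e = 0 and p = 0.7 returned 0.343, which matches 0.24/0.7. With e = 0.10 and p = 0.7 the formula gives 0.10 + 0.343 = 0.443.

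Both biases are proportional to h. If uptake is recorded in sessions and not scaled 0–1, the estimate is per session, but the whole intention-to-treat difference is still divided by education dose alone.

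**The case against.** The strongest reply is that this is a supplementary analysis, that uptake will be high, and that the protocol never calls the result an education effect. Much of that stands.

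- **Uptake.** The exclusion criteria remove children whose education setting does not agree to take part, and Procedures describes engagement work and payments to schools. Both may push p upwards. At p = 0.9 the package reading is off by only 0.03 SD. But Phase 2 itself expects variable compliance, and on the education reading high uptake does not rescue the estimate, because h/p cannot fall below h.
- **Estimand.** A reader might infer that the plan sets out to report an education-component effect, and so would announce a school benefit even if the school sessions did nothing. The text does not say so. It can equally be read as the package effect in children whose setting engaged. The exclusion restriction fails on that reading too, because poorly complying children still receive home therapy, but the bias is smaller.
- **Outcome.** A reader might also assume the CACE is for ADOS. No outcome is named. School-based measures would not remove the problem, since Phase 2 also tests a home-to-education route (paths a, b, c), but the figures based on 0.24 would not carry over.
- **Direction.** Upward bias is not automatic. It needs a beneficial home effect in education non-compliers. The 0.24 is printed with limits 0.59 and 0.11. Limits of −0.59 and 0.11 have midpoint −0.24, whereas 0.11 and 0.59 have midpoint 0.35, so a sign appears to have been lost and the interval probably includes zero.
- **Additivity.** The protocol regards joint parent–school work as key to generalisation, so home and education effects may interact. The formulas are then approximate.

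A last reply is that the analysis plan will settle this. The detail may sit there, but the protocol already states the exposure and the instrument, and that pairing is the fault.

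**Conclusion.** The point holds at moderate weight. As specified, the CACE needs an exclusion restriction that contradicts the protocol's account of what randomisation delivers and of how it may reach the outcome. The restriction fails whenever home therapy has an effect in children whose education setting complies poorly. How far the estimate is off depends on the reading and on p, as tabulated. Those figures rest on an illustrative h, an assumed range for p, additivity, and a home effect common to compliers and non-compliers.

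A reader might take this to undermine the trial's main result or its central generalisation question. The documents do not support that. The primary inference is the intention-to-treat ANCOVA, and generalisation is addressed by the mediation and structural equation models over paths a to f. Neither uses this CACE.

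**What to change.** For the CACE with randomisation as instrument, define compliance on receipt of the whole PACT-G package (parent plus LSA sessions), so that zero dose means no PACT-G. State the outcome and the exclusion restriction, and say that the result is not an education-specific effect.

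If an education-specific effect is wanted, report it as exploratory from a model that allows a non-zero effect in education non-compliers. There are two routes: principal stratification, or home dose and education dose as two exposures with the covariate-by-randomisation instruments that Phase 2 already names.

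The cost is mainly wording. Therapy compliance is already to be monitored (Training and fidelity of treatment), so no new data collection should be needed. There are two drawbacks. A combined session count treats parent and LSA sessions as interchangeable unless a weighting is justified. The education-specific estimate will be imprecise, and the interaction instruments may be weak with about 220 children analysed (110 per group).
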